### 4.1. Primary Outcome

The primary outcome is physical performance, assessed by the change in the Short Physical Performance Battery total score from baseline to the three-month assessment (time point). The SPPB is a well-validated tool ranging from 0 (worst) to 12 (best), assessing balance, gait speed, and lower limb strength. The change will be analyzed as a continuous variable, and the between-group difference will be expressed as the mean difference with a 95% confidence interval.

### 4.2. Secondary Outcomes

(1) Frailty status, assessed by the change in the Frailty Index score from baseline to the 3-month, 6-month, and 12-month assessments. The change will be analyzed as a continuous variable. Changes in frailty trajectories, as measured by the Frailty Index.

(2) Changes in intrinsic capacity: the intrinsic capacity is measured using the World Health Organization’s (WHO) Integrated Care for Older People (ICOPE) approach.

(3) Malnutrition risk assessment, measured by the Malnutrition Risk Assessment Form for older adults.

(4) Frailty recovery rates, defined as the proportion of participants transitioning from a frail to a pre-frail or robust state.

(5) Cognition function is evaluated using the Mini-Mental State Examination (MMSE).

(6) Sleep condition is evaluated using the Pittsburgh Sleep Quality Index.

(7) Participant satisfaction and acceptability are evaluated using a self-administered scale.

(8) Serum protein: serum total protein, albumin, and transferrin.

(9) Urine 8-hydroxyguanosine (8-oxo-Gsn): urine oxidation marker 8-hydroxyguanosine (8-oxo-Gsn) level.

(10) Serum inflammatory factors: C-reactive protein (CRP), interleukin-6 (IL-6), tumor necrosis factor-α (TNF-α), insulin-like growth factor-1 (IGF-1), C-X-C-motif chemokine 10 (CXCL10), and chemokine C-X3-C-based ligand 1 (CX3CL1) in serum using ELISA.

(11) Changes in serum differential metabolites: using nontargeted metabolomics methods to examine the changes in serum differential metabolites in each group before and after intervention and explore the mechanism of intervention.

(12) Changes in gut microbiota: using the 16S sequencing method to detect changes in gut microbiota and differential bacterial genera among groups.

### 4.3. Biological Sample Collection and Handling

Biological samples will be collected at baseline and upon completion of the three-month intervention following an overnight fast. Approximately 10 mL of venous blood will be drawn into serum separator tubes and allowed to clot at room temperature for 30 min, followed by centrifugation at 3000 rpm for 10 min to isolate serum. Concurrently, first-morning void urine samples (approximately 10 mL) will be collected by participants using sterile containers. The resulting serum and urine supernatant will then be aliquoted into 1.5 mL cryovials under standardized protocols. All aliquots will be immediately frozen and stored at −80 °C in the laboratory of Peking University School of Public Health until subsequent batch analysis.

Serum samples will be analyzed for inflammatory biomarkers—including CRP, IL-6, TNF-α, IGF-1, CXCL10, and CX3CL1—using commercially available ELISA kits. Non-targeted metabolomic profiling of serum will be conducted via liquid chromatography–mass spectrometry (LC-MS), while urinary 8-oxo-Gsn will be quantified using ultra-performance liquid chromatography–tandem mass spectrometry (UPLC-MS/MS). Gut microbiota composition will be assessed through 16S rRNA gene sequencing performed on fecal samples collected at home by participants using provided kits and returned to the laboratory under cold chain conditions.

Any residual biological samples will be destroyed after the completion of all planned analyses. The informed consent process includes explicit provision for obtaining participant permission regarding the future use of de-identified samples for additional research related to aging and nutrition.

### 4.4. Adverse Events

An adverse event (AE) is defined as any untoward medical occurrence in a participant during the study period, regardless of its causal relationship with the intervention. All AEs will be monitored throughout the study and systematically collected during the monthly health counseling, bi-weekly lectures, and at each assessment time point (3, 6, and 12 months) using open-ended questions and specific inquiries about common issues, such as falls, musculoskeletal pain, gastrointestinal discomfort, and allergies.

AEs will be graded for severity (mild, moderate, and severe) and their relationship with the intervention (unrelated, possibly related, and probably related) by the principal investigator. All AEs will be recorded in a standardized form. Serious adverse events (SAEs) will be reported to the PKU IRB within 24 h of awareness.

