### 3.1. Control Group

The control group will receive routine community health management only, which represents the standard level of care currently available for frail older adults in the community. This includes monthly health education lectures on general topics (e.g., chronic disease prevention), provision of standard health education materials, and access to basic health counseling services. Critically, the control group will not receive the study’s active intervention components, such as the personalized nutritional consultations, anti-inflammatory diet guidance, provision of protein powder and whole grains, structured exercise guidance, or the intensive bi-weekly health education lectures specific to frailty and malnutrition that are delivered to the intervention groups.

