### 3.2. Multifaceted Nutrition Intervention

In this group, a three-month multifaceted nutrition intervention will be conducted. All nutritional interventions and recommendations will be provided to participants based on professional discussions and reviews by nutrition experts from the School of Public Health at Peking University. The specific content is as follows:

(1) Daily dietary guidance: Participants will receive an anti-inflammatory dietary menu (Supplementary Table S1) designed based on the Chinese Dietary Guidelines for the Elderly (2022 Edition) and principles from the Dietary Inflammatory Index [32,33]. The diet emphasizes the intake of fruits, vegetables, whole grains, nuts, and fatty fish while reducing refined carbohydrates and saturated fats. Additionally, we will provide participants with a daily nutritional supplement containing 10 g of whey protein to address the high prevalence of sarcopenia in frail elders and support muscle protein synthesis [34], along with 50 g of whole grains to increase dietary fiber and phytochemical intake, which are associated with improved gut microbiota and reduced systemic inflammation [35,36].

(2) Personalized nutritional intervention: In response to specific health issues and diseases, we have established fixed consultation times at community hospitals, allowing elderly individuals to seek advice at designated intervals if they have health-related needs. Furthermore, we will offer on-demand online consultations with registered dietitians to promptly address the nutrition and health concerns of the elderly.

(3) Health education: Every two weeks, nutrition and health knowledge lectures (Table 2) will be conducted for elderly family caregivers and the elderly themselves, covering topics such as chronic diseases, malnutrition, and frailty.

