**Figure 3 nutrients-17-03213-f003:**
[figure not shown]
Training wheel chart.

**Table 1 nutrients-17-03213-t001:** Description of the intervention content for each group.

Group	Intervention Components	Personnel	Frequency
Control Group	1. Routine community health lectures - Health education lectures - Provision of health education materials - Health counseling services	Trained project staff	Monthly
Multifaceted Nutrition Intervention	1. Daily dietary guidance - Provision of anti-inflammatory diet recipes, cooking tips, and a guidebook - Daily provision of 10 g of whey protein powder and 50 g of whole grains	Trained nutrition specialists	Weekly
	2. Personalized nutritional consultations - Integration of fixed-time, in-person hospital consultations with on-demand online consultations	Intelligent app/programs	At any time
	3. Health education - Lectures on chronic diseases, malnutrition, and frailty	Trained nutrition specialists	Every two weeks
Multifaceted Nutrition and Exercise Combined Intervention	Includes all components from the Multifaceted Nutrition Intervention group, PLUS: 4. Exercise guidance - Provision of an exercise intervention manual and wheel chart - Distribution of elastic resistance bands for resistance exercises	Trained sports specialists	Weekly

**Table 2 nutrients-17-03213-t002:** Outline of the health education activities for the elderly.

**No.**	**Activities**	**Content (Lecture Theme)**
The first month		
1	Lecture 1	Nutritional Status and Common Health Issues in the Elderly
2	Lecture 2	Unlocking the Health Code: Understanding Nutrients
Qualitative interviews: satisfaction survey and feedback		
The second month		
3	Lecture 3	Unlocking the Health Code: Recognizing the Nutritional Value of Foods
4	Lecture 4	Focus on Nutritional Screening: How the Elderly Can Identify Malnutrition
Qualitative interviews: satisfaction survey and feedback		
The third month		
5	Lecture 5	How the Elderly Should Plan Their Three Meals a Day
6	Lecture 6	To Live Longer, Overcome ‘Physical Frailty’—A New Perspective on Elderly Health Management
Qualitative interviews: satisfaction survey and feedback		
The fourth month		
7	Lecture 7	A Healthy Life, ‘Muscle’ is Essential—Nutritional Management of Sarcopenia
8	Lecture 8	Scientific Diet: Helping You ‘Keep Your Memory’
Qualitative interviews: satisfaction survey and feedback		

**Table 3 nutrients-17-03213-t003:** Schedule of assessments and outcome measures.

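### Adverse events are also collected at two-weekly lectures that only the active arms attend, so up to month 3 controls have fewer scheduled occasions to report minor events

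*Protocol article*

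**What the plan says.** Section 4.4 names three kinds of occasion on which AEs are "systematically collected during the monthly health counseling, bi-weekly lectures, and at each assessment time point (3, 6, and 12 months". The questioning is partly open and partly prompted, and the prompts cover falls, musculoskeletal pain, gastrointestinal discomfort and allergies.

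The lectures are not common to the arms. Section 3.1 lists "the intensive bi-weekly health education lectures specific to frailty and malnutrition that are delivered to the intervention groups" among the components withheld from controls. Section 3.2, item (3), gives them to the nutrition arm: "Every two weeks, nutrition and health knowledge lectures (Table 2) will be conducted for elderly family caregivers and the elderly themselves". Table 1 gives the combined arm everything that the nutrition arm receives.

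Controls have lectures of their own: "This includes monthly health education lectures on general topics (e.g., chronic disease prevention". These are monthly, and section 4.4 names only the two-weekly ones. Controls also have "access to basic health counseling services". Table 1 lists "Health counseling services" in the control row alone, with a monthly frequency.

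The assessments at 3, 6 and 12 months apply to all three arms (sections 4 and 4.4, Table 3). Table 2 adds lectures 7 and 8 under "The fourth month", although the intervention lasts three months.

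**The concern.** A participant who is asked more often about recent minor complaints reports more of them. Of the three AE channels, the most frequent belongs to the active arms only. Nothing in the article evens out the contact, and nothing sets the common assessments apart as the basis for describing AEs by arm.

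The prompted events are those most open to this effect, since a passing ache or a minor fall is easily forgotten within weeks. They are also plausible harms of exercise, whey protein and whole grains. Better ascertainment in the treated arms could therefore look like a small tolerability problem. At stake is the description of comparative tolerability for a program that the authors present as scalable in frail older people.

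**Working it through.** The plan states no number of AE occasions per arm, so there is no figure to reproduce. The count follows from the schedule.

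**Scheduled occasions, baseline to month 3**

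- Control: 3 monthly counseling sessions (Table 1) + 1 assessment at month 3 = 4.
- Each active arm: 6 lectures (Table 2, months 1 to 3) + 1 assessment at month 3 = 7.
- Ratio: 7 / 4 = 1.75.

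These are nominal counts. The 4 assumes that controls take up counseling every month, which section 3.1 words only as access. The 7 assumes that every lecture is attended and that AE questions reach each person there. Section 3.4 keeps attendance logs for online and in-person lectures, so full attendance is not a given. The last lecture or counseling session may also fall close to the month-3 assessment. If the active arms also kept monthly counseling on separate dates, their count would be 6 + 3 + 1 = 10, but the article does not say so.

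**What this could do to event counts**

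The documents give no recall data, so the following is an illustration. Assume equal true event rates, events spread evenly between inquiries, and a chance of being reported that decays exponentially with half-life h weeks. With inquiries L weeks apart, the mean share captured is

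c(L) = (1 − exp(−kL)) / (kL), with k = ln 2 / h.

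Take L = 2 for the active arms and L = 13/3 = 4.33 for controls. The spurious rate ratio is c(2) / c(4.33). If half of all events are always captured (also assumed), it becomes (0.5 + 0.5·c(2)) / (0.5 + 0.5·c(4.33)).

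| h (weeks) | c(4.33) | c(2) | Ratio, months 0–3 | Ratio, half always captured |
|---|---|---|---|---|
| 2 | 0.518 | 0.721 | 1.39 | 1.13 |
| 4 | 0.703 | 0.845 | 1.20 | 1.08 |
| 8 | 0.834 | 0.918 | 1.10 | 1.05 |
| 26 | 0.944 | 0.974 | 1.03 | 1.02 |

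**Over the whole 12 months**

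After month 3 the named assessments are the same in all arms, with intervals of 13 weeks (to month 6) and 26 weeks (to month 12). Lectures 7 and 8 are left out because it is unclear whether they are held. Weighting by time, the capture over 52 weeks is

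[13·c(first) + 13·c(13) + 26·c(26)] / 52,

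where c(first) is c(2) in the active arms and c(4.33) in controls. For h = 2, c(13) = 0.220 and c(26) = 0.111, which gives 0.291 in the active arms and 0.240 in controls, a ratio of 1.21. For h = 4, 8 and 26 the ratios are 1.09, 1.04 and 1.01. With half of events always captured, the four ratios are 1.04, 1.03, 1.01 and 1.00.

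**The case against.** The strongest reply is that section 4.4 describes safety surveillance and not a comparison. AEs are not among the primary or secondary outcomes in sections 4.1 and 4.2, and section 4.6 names no AE analysis. Asking more often in arms that receive supplements and exercise is sensible for participant safety. All arms already share the 3-, 6- and 12-month questioning, and how AEs are tabulated is commonly left to the analysis plan. The bias also runs against the interventions, so it cannot create a false efficacy claim or hide harm in the active arms.

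Most of this stands, and it limits the weight of the point. It does not remove it. The unequal schedule is stated, not merely left open, and ascertainment is settled when the data are collected. A later analysis can rely on the common visits only if the questions there cover the whole interval and events already mentioned at a lecture are recorded again.

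A reader might infer that AE counts in the active arms would be inflated by 1.75, the ratio of occasions. The documents do not support that. The figure compares scheduled contacts, and recorded events need not rise in proportion. Nor are the extra events false: they are real events that are better ascertained, while controls are under-ascertained. A reader might also infer that the safety findings as a whole or the trial's main result are compromised. Serious, persistent or memorable events are likely to be reported under either schedule, and the month-3 SPPB comparison does not use AE reports.

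**Conclusion.** The point holds in a limited form. As written, scheduled AE questioning up to month 3 is about 4 occasions in controls and at least 7 in the active arms, if all are attended. Any by-arm tabulation of minor, recall-dependent events in the treatment period would tend to be higher in the active arms relative to controls.

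The direction follows from the schedule, provided that attendance does not cancel the difference. The size is unknown, because the ratios in the working rest wholly on assumed half-lives and an assumed share of always-remembered events. Over 12 months the effect is probably small. Lectures 7 and 8, if held, would add two active-arm occasions before month 6, but their status is uncertain and the conclusion does not depend on them. This is an inexpensive improvement to make and no threat to the trial's main conclusions.

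**What to change.** - At the 3-, 6- and 12-month assessments, ask every participant in all three arms the same structured AE questions about the whole interval since the last assessment. Record every event, whether or not it was already reported elsewhere.
- Record the source of each AE report (common assessment, lecture, counseling or other contact).
- Use the common-visit reports for any between-arm AE comparison, and show all AEs by source alongside for safety. Lecture reports continue to be collected, so surveillance loses nothing.
- State in section 4.4 which AE contacts apply to each arm.

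The cost is small, since these assessments are already planned for everyone. The downside is that some brief minor events drop out of the comparison: under the same assumed half-lives of 2 to 26 weeks, asking only at month 3 captures a share of 0.220 to 0.845 of the events in months 0 to 3. Recall prompted by earlier questioning at lectures may also leave some residual bias. Common interviews at months 1 and 2 would recover part of the lost events, at a cost of at most 2 × 210 = 420 short extra interviews in the active arms if controls are asked at their monthly counseling. They are optional and not part of the required change.

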### 4.5. Sample Size Estimation

The sample size calculation was based on the anticipated effect of the intervention on the change in the Short Physical Performance Battery (SPPB) score, which is the primary outcome of this trial.

Based on the results of previous randomized controlled trials [22,37], a multifaceted nutrition and exercise intervention is expected to yield a mean between-group difference of approximately 1.4 points in SPPB score change after 3 months, compared to the control group. The pooled standard deviation (SD) of the SPPB score change is estimated to be 2.5 points.

At α = 0.05, β = 0.1 and k = 3 were used. For a three-group superiority trial, the required sample size per group was calculated:$$n=\frac{(k-1)(Z_{1-\alpha /2}\;+\;Z_{1-\beta }{)}^{2}\times s^{2}}{\sum_{i=1}^{k}(\mu_{i}-\mu {)}^{2}}$$

Accounting for an anticipated 10% loss to follow-up, the sample size was increased to 105 participants per group, resulting in a total sample size of 315 participants.

### 4.6. Statistical Analyses

This study will employ the Intention-to-Treat (ITT) and Per-Protocol (PP) analysis sets to ensure that all randomized study subjects remain in their assigned groups. The Intention-to-Treat population will include all randomized participants, analyzed according to their assigned group. The Per-Protocol population will include only those participants who completed the intervention as prescribed and had no major protocol deviations. For missing quantitative data, the last observation carried forward method will be used. When the results of the ITT and PP analyses are consistent, the ITT results will be presented. When the results differ, the differences will be discussed. The variables will be analyzed using SPSS V.23.0 software. All statistical tests will be two-sided at the 5% level of significance. Continuous variables with a normal distribution will be shown as the mean and SD and those with an abnormal distribution will be presented as the median and IQR. Categorical variables will be expressed as a percentage or constituent ratio. Baseline characteristics will be presented for each group using descriptive statistics (means and standard deviations for normally distributed continuous data, medians and interquartile ranges for non-normally distributed data, and frequencies and percentages for categorical data). Mixed-model repeated-measures analysis of variance with adjustment for baseline characteristics will be performed for different measurement time points between groups, and interaction between groups and measurement time. For continuous outcomes, we will report the pre- and post-intervention means for the intervention and control groups, as well as the model-adjusted mean differences between groups. For binary outcomes, we will report the pre- and post-intervention percentages for the intervention and control groups, along with the adjusted odds ratios (ORs) between groups. The 95% confidence intervals (CIs) and associated *p*-values will be calculated. We will use nontargeted metabolomics methods to examine the changes in serum differential metabolites in each group before and after the intervention and explore the mechanism of intervention. We will use 16S rRNA gene sequencing to detect changes in gut microbiota and differential bacterial genera among groups. To address the second primary hypothesis regarding the potential mechanisms, correlation analyses (Spearman’s or Pearson’s correlation) and mediation analysis will be performed to examine the relationships between changes in clinical outcomes (SPPB score and frailty) and changes in biomarker levels (inflammatory markers and microbial abundance). Subgroup analyses will be conducted to investigate whether the effects of the intervention vary across different demographic and clinical subgroups.

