## Abstract

Background: The rapid aging of China’s population poses significant challenges, particularly in public health and medical services. Frailty, a reversible geriatric syndrome, is a critical intervention target for disability prevention among older adults. Objective: We hypothesize that both intervention groups will demonstrate significant improvements in Short Physical Performance Battery (SPPB) scores compared to the control group, and that these improvements will be accompanied by parallel reductions in inflammatory markers and beneficial alterations in the gut microbiota. Methods: The MultIfaceted NUtrition inTervention for frail Elderly (MINUTE) trial is a randomized, parallel-group controlled trial. In Beijing, China, 315 frail older adults were recruited and randomly assigned to 3 groups: a control group receiving routine community health management only, multifaceted nutrition intervention group, and a multifaceted nutrition and exercise combined intervention group, each comprising 105 participants. The study consists of a three-month intervention period followed by a nine-month follow-up. During the three-month intervention period, the control group receives routine community health management, while the multifaceted nutrition intervention group receives daily dietary guidance, personalized nutrition consultations, and health education. Additionally, the combined intervention group receives exercise interventions in addition to the nutritional components. After the three-month intervention, all three groups will be followed up for nine months to assess the sustainability of the study. Results: The primary outcomes are the changes in the SPPB scores. The secondary outcomes include frailty scores, intrinsic capacity, malnutrition risk, frailty recovery rates, serum differential metabolites, inflammatory factors, and gut microbiota changes. This study aims to establish a scalable and sustainable pathway for frailty prevention among community-dwelling older adults in China and provide valuable insights to inform strategies for healthy aging. Trial registration: This study is conducted in accordance with the Declaration of Helsinki and approved by the Peking University Institutional Review Board (IRB00001052-23178) on February 3, 2024, with all amendments subject to prior review and approval. Informed consent is obtained from participants, and findings will be disseminated through peer-reviewed publications, conference presentations, and summaries for school staff and participants. ClinicalTrials.gov (NCT06547593) registered 30 July 2024.

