## 4. Outcomes

Table 3 describes the study outcomes, including when and how the study outcomes will be evaluated. Baseline measurements will be conducted for all three groups. Follow-up measurements will be conducted at 3 months (end of intervention), 6 months, and 12 months (end of follow-up) after the baseline measurement. The primary and secondary outcomes will be assessed by comparing changes from baseline within and between groups.

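### LOCF scores every participant missing at month 3 as zero SPPB change and carries the month-3 score forward for anyone last seen then; the bias is modest at the planned 10% loss but avoidable

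*Protocol article*

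**What the plan says.** Section 4.6 (Statistical Analyses) gives a single missing-data rule for continuous outcomes: "For missing quantitative data, the last observation carried forward method will be used". It applies to an analysis set defined in the same section: "The Intention-to-Treat population will include all randomized participants, analyzed according to their assigned group". The model named there is also a repeated-measures one: "Mixed-model repeated-measures analysis of variance with adjustment for baseline characteristics will be performed for different measurement time points between groups", with a group-by-time interaction.

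The visit schedule is in Section 4 (Outcomes): "Follow-up measurements will be conducted at 3 months (end of intervention), 6 months, and 12 months (end of follow-up) after the baseline measurement". Table 3 shows the same four time points for each SPPB component. Section 4.1 defines the primary outcome as physical performance, "assessed by the change in the Short Physical Performance Battery total score from baseline to the three-month assessment", to be reported as a between-group mean difference with a 95% confidence interval. The Abstract gives the purpose of the later visits: "After the three-month intervention, all three groups will be followed up for nine months to assess the sustainability of the study".

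**The concern.** Read together, the rule and the schedule fix what gets imputed.

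- **Month 3 (primary).** No SPPB visit lies between baseline and month 3, so baseline is the only value that can be carried forward. Every month-3 absentee in the all-randomized set is entered as a change of 0. This includes someone who returns at month 6, whose later score LOCF ignores when filling month 3.
- **Months 6 and 12.** Anyone last seen at month 3 has the end-of-intervention score entered at both later visits. For those participants the rule assumes the persistence that the follow-up is meant to test.
- **Precision.** The imputed values are analysed as if observed. A block of exact zeros at month 3 shrinks the SD of change, and full sample size is credited, so the standard error is too small.

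At stake are the primary mean difference, its confidence interval, and the reading of the 6- and 12-month SPPB data. The Frailty Index, a secondary outcome at 3, 6 and 12 months (Section 4.2), falls under the same rule.

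**Working it through.** **Inputs from the protocol.** Difference 1.4 points for the combined intervention against control, SD of change 2.5, loss 10%, 105 per group (Section 4.5); two-sided 5% tests (Section 4.6). The article gives no figure for the effect of missing data, so there is none to reproduce. The 105 is taken as given; how it was derived is a separate matter and does not enter here.

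**Assumptions.** The split of the 10% by arm and by visit is not stated. Unless noted, loss is equal by arm, dropouts resemble completers, and the control change is 0.

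**1. Month-3 estimate.** With loss d_t (treated) and d_c (control), expected LOCF difference = (1 − d_t) × change_t − (1 − d_c) × change_c.
- 10% in both arms: 0.90 × 1.4 = 1.26, bias −0.14. With equal loss this does not depend on the control change.
- 20% in both arms (assumed, double the plan): 0.80 × 1.4 = 1.12, bias −0.28.
- 15% treated, 5% control (assumed): 0.85 × 1.4 = 1.19 with control change 0; 1.14 to 1.24 for control changes of +0.5 to −0.5.

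**2. Month-3 SD and coverage.** Variance of the LOCF change in an arm with mean m and loss p is (1 − p) × 2.5² + p(1 − p) × m².
- Control, p = 0.10, m = 0: 5.625, SD 2.37.
- Treated, p = 0.10, m = 1.4: 5.625 + 0.09 × 1.96 = 5.80, SD 2.41.
- LOCF standard error: √((5.625 + 5.80)/105) = 0.33. From the roughly 94.5 per arm actually observed it is 2.5 × √(2/94.5) = 0.36.
- In 20,000 simulated trials with loss at random, the 95% interval covered 1.4 in 92.5% of trials under LOCF at 10% loss and in 85.0% at 20%. Analysis of the observed values gave 94.8% and 95.0%, with a mean estimate of 1.40.

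**3. Month-3 direction.** Suppose 15% of treated and 5% of control participants leave, and leavers truly change by −1.5 (assumed).
- True all-randomized difference: (0.85 × 1.4 − 0.15 × 1.5) − (0 − 0.05 × 1.5) = 0.965 + 0.075 = 1.04.
- LOCF: 0.85 × 1.4 − 0 = 1.19, an error of +0.15 in favour of the intervention.

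**4. Month 12.** Let r be the share of the 1.4 gain truly kept and d the share last seen at month 3. LOCF difference = (1 − d) × r × 1.4 + d × 1.4. Rejection rates use SE = 2.5 × √(2/105) = 0.345, which assumes that the SD of 2.5 also holds at month 12.

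| Gain kept | d | True | LOCF | Two-sided rejection |
|---|---|---|---|---|
| none | 5% | 0 | 0.07 | 5.5% |
| none | 10% (all planned loss) | 0 | 0.14 | 6.9% |
| none | 20% (assumed) | 0 | 0.28 | 12.8% |
| half | 10% | 0.70 | 0.77 | – |
| all | any | 1.40 | 1.40 | – |

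The month-3 and month-12 figures draw on the same 10%. If all of it goes before month 3 and never returns, baseline is carried throughout and nothing is frozen at the month-3 level. With an even split, month 3 gives 0.95 × 1.4 = 1.33 and month 12, with the gain fully faded, gives 0.07.

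**The case against.** The best defence is size. At the plan's own loss, equal by arm and with dropouts like completers, the error is at most 0.14 points at either visit, and it cannot be 0.14 at both. Pairwise power is unharmed: about 97% with LOCF (1.26 points, SD 2.39, 105 per arm) and about 97% with 94 completers per arm. That stands; the damage is to the estimate and interval, not to the chance of a significant result.

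Further points also stand. The primary outcome is at month 3, and SPPB at 6 and 12 months is scheduled in Table 3 but is not in the secondary list of Section 4.2. Someone seen at month 6 carries that value, not the month-3 one. Missing-data sensitivity analyses are commonly left to an analysis plan, so their absence from the article is not a fault.

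Four stronger readings are tempting but unsupported:
- *LOCF will manufacture persistence at month 12.* It does so only for those last seen at month 3, and only if the gain fades.
- *False-positive rates near 13% should be expected.* That needs 20% last seen at month 3, twice the total loss in Section 4.5.
- *The exercise arm will lose more people.* The Introduction mentions difficulty with exercise adherence, which is not loss to follow-up, and Section 3.3 adds support for participants.
- *The plan already has a missing-at-random analysis.* The wording "Mixed-model repeated-measures analysis of variance with adjustment for baseline characteristics will be performed" does not say that the fit is by likelihood.

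The defence that LOCF is at least conservative does not stand, because step 3 gives an error in the intervention's favour.

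**Conclusion.** The concern holds as a flaw in a stated rule, modest in size at the planned loss. LOCF imputes a change of 0 for every participant missing at month 3 and carries the month-3 score forward for those last seen then. With 10% loss before month 3, 1.40 is estimated as 1.26 with about 92.5% coverage; this rests on equal loss and dropouts like completers, and the sign can reverse otherwise. With the whole 10% last seen at month 3 and the gain gone by month 12, a true 0 is reported as 0.14 and the nominal 5% test rejects about 7% of the time. There is no month-12 bias if the gain is kept.

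A reader might infer that the primary conclusion is at risk or that the sustainability result will be spurious. The article supports neither, since it does not give loss by arm and visit and power is essentially unchanged. The case for change is that the rule harms the estimate and interval promised in Section 4.1, and builds in persistence where persistence is the question, when a better analysis is close to the one already named.

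**What to change.** Delete the LOCF sentence from Section 4.6. State that the repeated-measures mixed model is fitted by REML to all observed SPPB values, by randomized group, with group, visit and group-by-visit terms, and that the month-3 contrasts with control are the primary result.

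A model of post-baseline scores with baseline SPPB only as a covariate would drop anyone with no post-baseline visit, against the all-randomized definition of the analysis set. Keep them in one of two ways: enter baseline SPPB as a response with a mean common to the three groups (and then not also as a covariate), or use multiple imputation. Add a delta-adjusted multiple imputation, with the shift varied by arm, as a sensitivity analysis for data missing not at random. Use the same approach for the other continuous outcomes measured at several visits.

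The cost is analysis wording and one extra analysis to programme; no visit, sample or procedure changes. The primary analysis would then rely on data being missing at random, which cannot be verified and is the reason for the sensitivity analysis. Section 2.4 keeps the data analysts blinded, so the change should be made and dated before unblinding.
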